## **10**      **Statistics**

### **10.1**      **Sample Size Determination**

Sample size determination for this study is based on 2-sided t-tests with a global alpha level of 5% and a statistical power of 90%. A standard deviation of 20 dB for the test statistic is assumed. In order to be able to confirm a treatment difference of 15 dB PTA of active treatment versus placebo with a 2:1 randomization, a total number of 87 evaluable patients will be required, 58 patients in the group receiving ancrod, and 29 patients receiving placebo. To compensate for dropouts, a total number of 99 patients is planned to be enrolled, 66 patients receiving ancrod, and 33 patients receiving placebo.

### **10.2**      **Statistical Methods**

The statistical analysis will be conducted following the principles as specified in the effective ICH Guideline (ICH E9). Complete details of the statistical analyses and methods, including data conventions, will be described in a separate statistical analysis plan (SAP) which will be finalized before unblinding.

For all variables measured at the randomization visit (day 1; visit 1) the last available value prior to the first intake of study medication will be considered as the baseline value. The primary endpoint value is the value measured at day 8 (visit 5).

All efficacy and safety variables will be summarized by treatment group using descriptive statistics (mean, standard deviation [SD], median, minimum, and maximum for continuous data and absolute and relative frequencies for categorical data). Data will be summarized for baseline, endpoint and by visit. The level of significance will be  $\alpha = 0.05$ .

|                                |                             |                      |
|--------------------------------|-----------------------------|----------------------|
| Protocol Amendment 7.1         | Study no.: NM-V-101         | Page 57 of 85 |
| Date of Amendment: 15 Feb 2018 | EudraCT No.: 2012-000066-37 |                      |

### 10.2.1 Method to Evaluate the Primary Efficacy Measure

The primary analysis will be based on the intent-to-treat population (full analysis set); in addition, a per protocol analysis (excluding patients not fulfilling the evaluability criteria) will be done.

Evaluability criteria are:

- Have SSHL as defined per inclusion criterion 1
- Provide valid PTA data (Air) for Visit 1 and Visit 5
- Adhere reasonably well to the study protocol without major protocol deviations.

Last-observation-carried-forward (LOCF) will be applied for post-baseline measurements. An analysis of covariance (ANCOVA) model with treatment as fixed effect, center as random effect, and baseline PTA as covariate will be calculated. According to the data structure, it may be advisable to analyze the differences endpoint minus baseline value with a general linear model (GLM).

Underlying assumptions, such as normality and homogeneity of variance will be assessed. Should these assumptions be violated, appropriate data transformations or the choice of a non-parametric analysis method will be considered. Baseline comparability will be evaluated based on pooled data from all study sites. To determine comparability of the ancrud and placebo groups at baseline, demographic and pre-treatment characteristics that are continuous will be analyzed by general linear model (GLM). If treatment group differences are seen at the 0.10 level of significance, these variables may be added as stratification variables or covariates to the efficacy analyses.

All randomized participants in the analysis will be grouped according to their originally assigned treatment.

### Additional Analyses of Primary Outcome Measure

The mean change at the affected frequencies will be classified into the following categories:

| Definition* | Improvement                                                                                                                                                                                                          |
|-------------|----------------------------------------------------------------------------------------------------------------------------------------------------------------------------------------------------------------------|
| Recovery    | Hearing level recovers within 30 dB at 250, 500, 1000, 2000 Hz and within 25 dB at 4000 Hz, or
Hearing level recovers to that of contralateral intact ear if hearing in intact ear can be considered to be stable |
| Good        | Average hearing improvement for five frequencies $\geq 30$ dB                                                                                                                                                        |
| Fair        | Average hearing improvement for five frequencies $\geq 10$ and $\leq 30$ dB                                                                                                                                          |
| No change   | Average hearing improvement for five frequencies is within 10 dB                                                                                                                                                     |

\*Hearing recovery as defined by the Ad Hoc Committee of the Ministry of Health and Welfare in Japan

|                                |                             |                      |
|--------------------------------|-----------------------------|----------------------|
| Protocol Amendment 7.1         | Study no.: NM-V-101         | Page 58 of 85 |
| Date of Amendment: 15 Feb 2018 | EudraCT No.: 2012-000066-37 |                      |

A comparison of mean changes of participants who completed the study will be made. Multiple linear regression analysis will be performed to evaluate the magnitude of the treatment effects after adjustment for participant characteristics such as age, gender, duration of SSHL prior to treatment, and baseline degree of hearing loss. The response and characteristics of participants who do not complete treatment will be evaluated to assess the missing response pattern.

The mean changes in PTA will be compared for the following subgroups:

- Gender (males or females)
- Degree of SSHL
- SSHL with or without associated vestibular symptoms
- Presence of tinnitus
- Age (above vs. below median, quartiles)
- Status of the contralateral ear
- Duration of SSHL before start of treatment (above vs. below median)
- Baseline fibrinogen level ( $\leq 360$  mg/dL;  $>360$  mg/dL, quartiles)
- Use of rescue medication.

In addition, the effect of diabetes mellitus, hypertension, and ischemic heart disease will be included in the analysis.

Because the study is not powered to detect significant treatment effects in subgroups, the limitations of drawing conclusions if no treatment effect is observed in a subgroup is recognized.

### **Methods to evaluate Secondary Efficacy Measures**

The quantitative parameters will be analyzed in analogy to the primary efficacy variable. For 2x2-tables, the qualitative parameters will be analyzed with the exact Fisher-test; the Freeman-Halton test will be used for tables that are larger than 2x2 and if a table is very large, analysis will be carried out with the asymptotic chi-square-test.

The semi-quantitative parameters patient and physician assessment of change of hearing ability will be transformed to three qualitative categories. Further details and analyses depend on the CRF structure and will be described in detail in the Statistical Analysis Plan.

### **Safety Measures**

|                                |                             |               |
|--------------------------------|-----------------------------|---------------|
| Protocol Amendment 7.1         | Study no.: NM-V-101         | Page 59 of 85 |
| Date of Amendment: 15 Feb 2018 | EudraCT No.: 2012-000066-37 |               |

Safety data will be analyzed descriptively by treatment group. Absolute and relative frequencies will be calculated for AEs by system organ class and preferred term. The comparison of AEs between groups will be done by the exact Fisher test.

### **10.2.2 Expected Side Effects**

Reports of bleeding AEs, as well as major bleeding, will be identified and summarized through Day 90 after initiation of study drug. Bleeding AEs will be identified using the standard MedDRA query for hemorrhages. A logistic model will be used to test for treatment group differences in the incidence of major bleeding. The logistic regression model will include terms for treatment group, age, baseline fibrinogen level, and severity of SSLH.

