## 2.4 Potential Risks and Benefits

### 2.4.1 Potential Risks

Due to its mode of action, bleeding may occur during ancrod treatment. The direct effect of ancrod on the coagulation cascade and on platelet function may cause microscopic hematuria, bleeding at puncture sites, bruising and, in rare cases, melena, epistaxis, and hematemesis (Latallo, 1983). Many bleeding adverse events are related to bruising and are of limited clinical significance. The

|                                |                             |                      |
|--------------------------------|-----------------------------|----------------------|
| Protocol Amendment 7.1         | Study no.: NM-V-101         | Page 23 of 85 |
| Date of Amendment: 15 Feb 2018 | EudraCT No.: 2012-000066-37 |                      |

bleeding risk appears to be increased when fibrinogen levels remained below 40 mg/dL for longer periods.

The relatively high incidence of adverse events observed in clinical studies in patients with acute ischemic stroke treated with ancrod may be attributed to advanced age, predisposition, and vulnerability of this patient population and cannot be extrapolated to patients with sudden hearing loss who will be treated with a different, moderate dosing regimen. Further, the incidence of adverse events observed in the direct comparison of defibrinogenation therapy with corticosteroid revealed no minor or major bleeding. Side effects were observed in 84.9% of patients who received defibrinogenation therapy and in 85.9% of patients who received corticosteroid treatment (Kubo et al., 1988).

Local reactions, such as urticaria and exanthema, are rare but may occur after subcutaneous use. Some patients who had received ancrod subcutaneously developed local irritation or itching. These skin reactions have responded to antihistamine therapy. There was no evidence of an allergic reaction in healthy subjects or in patients treated with ancrod repeatedly. Nevertheless, special attention should be paid to patients receiving a second course of ancrod because neutralizing antibodies may occur particularly after long-term subcutaneous administration.

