### 10.1. Adverse Events

All adverse events (AEs) as recorded in the CRF module "Adverse Events" will be analyzed. Initially, an overview will be generated tabulating the number and percentage of patients (and the total number of events) with

- adverse events
- treatment-emergent AEs (for definition, see Section 4.3)
- treatment-emergent AEs with causal relationship (to IMP) given as 'Yes', or missing  
Note: When the answer to causality is not specified the AE will be analyzed as IMP-related
- treatment-emergent AEs leading to discontinuation ('Measures' is 'Treatment stopped')
- serious treatment-emergent AEs
- serious treatment-emergent AEs with causal relationship ('Causality' as above)
- serious treatment-emergent AEs leading to discontinuation ('Measures' as above).

For each category, AE rates of both treatment groups will be compared by Fisher's exact test.

Adverse events are coded according to the MedDRA terminology as described in the DMP. The following summaries for adverse events will be provided broken down by System Organ Class (SOC) and Preferred Term within SOC, separately for each treatment group:

- All treatment-emergent AEs (TEAEs)
- All TEAEs by maximum intensity ('Mild', 'Moderate', 'Severe', 'Life threatening', 'Death')
- All TEAEs related to IMP ('Causality' is given as 'Yes' or missing)
- All TEAEs leading to discontinuation ('Measures' is 'Treatment stopped')
- All TEAEs by action taken ('None', 'Treatment stopped', 'Dose reduced', 'Other treatment', 'Hospitalization') [1]
- All TEAEs by outcome ('Disappeared', 'Ongoing', 'Sequelae', 'Unknown', 'Death')
- All serious TEAEs

- All serious TEAEs related to IMP (causality as above)
- All serious TEAEs leading to discontinuation (measures as above).

[1] In case multiple responses per event are given, the event is counted for each response.

These summaries will generally provide the number and percentage of patients with TEAEs (and the total number of events) within each preferred term and within each SOC. Patients are counted only once for each preferred term when they have more than one AE with the same preferred term. Patients with more than one AE within a SOC will be counted for each corresponding preferred term within the SOC, but are counted only once for the SOC. The number of patients with at least one TEAE and the total number of events will also be displayed.

All tabulations will be sorted alphabetically by SOC and by frequency of preferred terms within each SOC.

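### The SAP omits the protocol's bleeding summary and test without declaring it, so patients with any bleed per arm appear in no planned table; restoring the logistic model is a poor remedy at the expected size

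*Combined protocol and SAP*

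**What the plan says.** Protocol 2.4.1 names bleeding as the first risk: "Due to its mode of action, bleeding may occur during ancrod treatment". It lists microscopic haematuria, puncture-site bleeding, bruising, melaena, epistaxis and haematemesis.

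Protocol 10.2.2 contains only the bleeding analysis. It makes three commitments:
- Identification: "Bleeding AEs will be identified using the standard MedDRA query for hemorrhages".
- A summary of bleeding AEs and of major bleeding through Day 90.
- A test: "A logistic model will be used to test for treatment group differences in the incidence of major bleeding", with terms for treatment, age, baseline fibrinogen and hearing-loss severity.

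SAP 10.1 plans an overview of AE categories (any, treatment-emergent, related, leading to discontinuation, serious), each compared by Fisher's exact test. Beyond that, "The following summaries for adverse events will be provided broken down by System Organ Class (SOC) and Preferred Term within SOC". A patient with several events in one organ class is counted under each preferred term and once for the class. The end-of-text tables in SAP 13.2 include no bleeding output. SAP Section 2 lists departures from the protocol, down to a chi-square test that is not needed, but not this one. SAP 9.3 covers additions only.

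**The concern.** Ancrod works by lowering fibrinogen, so bleeding is the harm expected from its mechanism, and safety is a stated secondary objective. The bleeding types in Protocol 2.4.1 arise in different organ systems and will be coded to different preferred terms in several organ classes. Adding up rows double-counts a patient who has both bruising and haematuria, so the planned tables cannot give the number of patients per arm with any bleed. Someone would have to rebuild it from the AE listings after unblinding, with no pre-specified term list.

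Two features increase the reliance on reported bleeding. SAP 5.4 says there is no data monitoring committee. Protocol 9.1.1 excludes abnormal fibrinogen and clotting times from AE recording.

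The obvious repair is to put the protocol's logistic model back, so it must be asked whether that model would work with the number of patients expected.

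**Working it through.** **Sample size.** Protocol 10.1 states: "A standard deviation of 20 dB for the test statistic is assumed"; the aim is to "confirm a treatment difference of 15 dB PTA of active treatment versus placebo with a 2:1 randomization"; and "a total number of 87 evaluable patients will be required". With two-sided 5% alpha and 90% power, placebo n = (1 + 1/2) × (1.960 + 1.282)² × (20/15)² = 28.02, rounded up to 29, so 58 + 29 = 87. Power of the t-test at 58/29 is 90.3%. With the 12% dropout in SAP 5.3, 87/0.88 = 98.9, so 99 (66:33). The stated figures reproduce, but they concern hearing only. No bleeding rate, event count or power is given.

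**Inputs for bleeding.** SAP Section 2 expects total enrolment only slightly above the 30 evaluable patients set for the interim analysis. I take 22:11 as the central case (assumption; 20:10 to 24:12 as the range) and compare it with the planned 66:33. Major-bleeding rates are assumed over a wide range.

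**Empty arm.** If either arm has no event, the treatment log-odds ratio has no finite maximum-likelihood estimate. With n₁, p₁ for ancrod and n₀, p₀ for placebo:

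P(empty arm) = 1 − [1 − (1 − p₁)^n₁] × [1 − (1 − p₀)^n₀]

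At 22:11 with 10%/2%: 0.90²² = 0.0985 and 0.98¹¹ = 0.8007, so P = 1 − 0.9015 × 0.1993 = 0.820. At 20:10 it is 0.839, at 24:12 it is 0.802 and at 66:33 it is 0.514.

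**Full four-term model.** A separation check was run on 1,000 simulated trials per scenario. The three covariates were independent standard normal variables unrelated to bleeding. Expected events are n₁p₁ + n₀p₀.

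| Rates, ancrod/placebo | Events, 22:11 | Empty arm | No finite solution | Events, 66:33 | Empty arm | No finite solution |
|---|---|---|---|---|---|---|
| 3%/1% | 0.8 | 95% | 95% | 2.3 | 76% | 75% |
| 5%/2% | 1.3 | 87% | 89% | 4.0 | 53% | 54% |
| 10%/2% | 2.4 | 82% | 83% | 7.3 | 51% | 52% |
| 20%/5% | 5.0 | 57% | 57% | 14.9 | 18% | 19% |
| 30%/10% | 7.7 | 31% | 32% | 23.1 | 3% | 4% |
| 40%/20% | 11.0 | 9% | 10% | 33.0 | 0.1% | 0% |

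The simulation tracks the empty-arm formula closely, so the empty arm is almost the whole problem.

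**What an exact comparison offers at 22:11.** With 0/11 on placebo, two-sided Fisher p is 0.067 at 7/22 on ancrod and 0.031 at 8/22, so significance needs at least 8/22 (36%). Power is about 0.1% at 10%/2% and 3% at 20%/5%. The exact interval is more informative: for 0/22 the upper 95% limit is 1 − 0.025^(1/22) = 15.4%, and for 0/66 it is 5.4%.

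**The case against.** The SAP is not silent on AEs by arm. Every preferred term is tabulated by arm, also by intensity, relatedness, action and outcome. A serious bleed enters the Fisher-tested serious category, its own table and the serious-event listing. All AEs are MedDRA-coded and listed by treatment, and SAP 13.6 allows further in-text tables on request. This stands. A reader might infer that there is no group comparison at all, or that the safety objective cannot be reported. The documents do not support either reading. What is missing is the bleeding-specific grouping, its pre-specification and its comparison.

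A reader might also infer that the protocol's model cannot be fitted. That does not follow. No major-bleeding rate is given, and at 30%/10% only about a third of trials at 22:11 fail. Protocol 10.2.2 does not name the fitting method, so penalised or exact logistic regression is not excluded. Nor can one say that the bleeding rows will be nearly empty: Protocol 2.4.1 notes that many bleeding events are bruising, so they may cluster in one term.

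Two limits apply to what can be checked. Part of SAP 4.3 (derived variables) was not in the text available for this review. A bleeding flag defined there would still have no output table in 13.2. The SAP is based on Protocol Amendment 7.0 and the protocol text is 7.1, so the 7.0 wording of 10.2.2 cannot be seen.

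**Conclusion.** The omission is established on the available text: Protocol 10.2.2 promises a bleeding summary, a major-bleeding summary and a test, and the SAP provides and declares none of them. The consequence is specific. Patients with any bleed, by arm, appear in no planned table, although the data to derive the number will exist.

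The case against simply reinstating the logistic model is conditional. If major bleeding is uncommon (3–10% on ancrod, 1–2% on placebo), ordinary maximum likelihood fails in about 83–95% of trials at 22:11 and in about 52–75% at 66:33. It becomes dependable only if major bleeding is common. These figures rest on assumed rates, an assumed final size and unrelated covariates.

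One further gap: neither document defines major bleeding in the available text, so that endpoint cannot be programmed as it stands. This should be corrected before unblinding. It does not affect the primary efficacy analysis.

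**What to change.** - Add to SAP 10.1 and 13.2 one Safety Set table, by arm, of patients with any AE in the haemorrhage query and patients with major bleeding, from first dose through Day 90. State the window explicitly: a restriction to treatment-emergent events matches the protocol only if that definition reaches Day 90.
- Give counts, exact 95% confidence intervals per arm and for the risk difference, and Fisher's exact p labelled exploratory. Fisher's test is already the protocol's method for comparing AEs.
- The sponsor states its definition of major bleeding, and the MedDRA query version and scope, before unblinding.
- Replace the logistic model by this exact comparison and record the change, with the reason, in SAP Section 2. Confirm the wording of 10.2.2 in Amendment 7.0.

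The cost is one table and a few lines of text on data already being coded. Covariate adjustment is given up. The Fisher test has very little power at this size, so interpretation should rest on the counts and intervals, and a non-significant p-value should not be read as evidence of no excess bleeding.

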### **10.2.3 Interim Analysis**

The recruitment of the patients will take a longer period than initially expected. For this reason a comparison of groups will be performed as interim analysis for the primary objective if 30 evaluable patients are included in the study.

## **11 Quality Control (QC) and Quality Assurance (QA)**

### **11.1 Study Monitoring and Auditing**

Monitoring and auditing procedures developed or endorsed by the Sponsor will be followed in accordance with GCP guidelines. Direct access to the on-site study documentation and medical records must be ensured.

#### **11.1.1 Study Monitoring and Source Data Verification**

Monitoring will be done by personal visits from a representative of the Sponsor or CRO (clinical monitor) that will check the CRFs for completeness and clarity, and crosscheck them with source documents (100% source data verification). Questionnaires completed by patients will be included in the CRF, and there will be no other source documentation available. In addition to the monitoring visits, frequent communications (letter, telephone, and fax) by the clinical monitor will ensure that the investigation is conducted according to protocol design and regulatory requirements.

Study close-out will be performed by the clinical monitor upon closure of the study.

|                                |                             |                      |
|--------------------------------|-----------------------------|----------------------|
| Protocol Amendment 7.1         | Study no.: NM-V-101         | Page 60 of 85 |
| Date of Amendment: 15 Feb 2018 | EudraCT No.: 2012-000066-37 |                      |

### **11.1.2 On-Site Audits**

Domestic and foreign regulatory authorities, the EC or IRB, and an auditor authorized by the sponsor may request access to all source documents, CRFs, and other study documentation for on-site audit or inspection. Direct access to these documents must be guaranteed by the investigator, who must provide support at all times for these activities. Medical records and other study documents may be copied during audit or inspection provided that patient names are removed on the copies to ensure confidentiality.

